**Yoga-based intervention**			
	Yoga practices (sessions 1-10)	Body postures (asanas), breathing techniques (pranayama), meditation, and relaxation exercises	60-90 min per session
	Final assessment (after the intervention)	QoLI, and self-report feedback on intervention experience	60 min

^a^QoLI: Quality of Life Inventory.

#### Data Monitoring

A data safety monitoring board (DSMB) will monitor data collection and protocol compliance. These will include interim analyses, if necessary, with predetermined termination procedures if safety issues or important emerging reported adverse events (AEs) call for study termination earlier.

Given the low-risk nature of the interventions (VR-assisted CBT [VR-CBT] and yoga) and the absence of pharmacological components, a formal independent data monitoring committee is not deemed necessary for this study. Both interventions are noninvasive, well-established, and widely used in clinical and wellness settings, minimizing the likelihood of severe AEs requiring external oversight. Instead, a DSMB will be responsible for overseeing participant safety, protocol adherence, and interim data reviews. The DSMB will be composed of 3 independent experts, including a clinical psychologist specializing in anxiety disorders, a statistician, and a researcher with expertise in VR interventions, ensuring multidisciplinary oversight from our team. This board will meet at prespecified intervals (eg, the midpoint and end of the study) to evaluate participant retention, dropout rates, and any reported adverse effects, such as cybersickness from VR exposure or physical discomfort from yoga sessions.

This study uses a systematic approach to collecting, assessing, reporting, and managing AEs and unintended effects related to the interventions. Given the noninvasive nature of VR-CBT and yoga, AEs are expected to be minimal, but potential risks such as cybersickness (VR-CBT), physical discomfort or strain (yoga), or emotional distress (both interventions) will be monitored. Participants will be instructed to report any AEs immediately during or after intervention sessions either verbally to facilitators or via structured postsession feedback forms. Solicited AEs will be actively monitored through weekly check-ins, while spontaneous reports will be recorded in an AE log maintained by the research team. The severity of reported events will be classified as mild (transient discomfort), moderate (requires temporary intervention modification), or severe (necessitates withdrawal from the study). In the event of a significant or unexpected AEs, the study team will conduct a risk-benefit assessment, and if necessary, the DSMB will review the case. Participants experiencing persistent distress or injury will be referred to appropriate clinical support services. All AEs and responses will be documented, reviewed in regular safety meetings, and included in the final study report, ensuring transparency and participant safety.

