**Methods:**

A single-blinded randomized controlled trial will be conducted with 60 participants (n=30, 50% per intervention group) recruited from university and preuniversity counseling centers. The trial will measure whether the interventions reduce performance anxiety in students. Stratified randomization will be used to ensure equal distribution of baseline anxiety levels and gender across both groups. The primary outcome is a reduction in anxiety, measured using the State-Trait Anxiety Inventory-Y1 and State-Trait Anxiety Inventory-Y2 subscales. Secondary outcomes include emotional regulation and quality of life. Data will be collected at baseline, after the intervention, and during follow-up assessments. Statistical analyses will include parametric tests (eg, repeated-measures ANOVA and *t* tests) to compare anxiety reduction, emotional regulation, and quality of life across groups. The intention-to-treat approach will be applied to minimize bias due to participant dropouts. Sensitivity analyses will assess the robustness of the findings.

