The participants will then start the psychoemotional support program and complete an anxiety level assessment at the end of each intervention session. At the end of the program, participants will complete the anxiety questionnaire again, along with an instrument assessing their comfort, discomfort, and the quality of the specific intervention techniques. To evaluate manifestations of performance anxiety, correlations between clinical anxiety and academic anxiety will be checked to indicate the strength and significance of their relationship. Details about the implementation of the techniques are presented in Table 1.

**Table 1 table1:** Overview of intervention components for virtual reality (VR)–assisted cognitive behavioral therapy (VR-CBT) and yoga-based interventions.

Intervention and phase		Session components	Duration

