### Data Analysis and Handling Missing Data

The analysis involves the use of advanced data management and statistical analysis software (eg, SPSS Statistics [IBM Corp] and Amos [IBM Corp]), and comparisons will be made between intervention groups using parametric statistical tests (eg, *t* tests and longitudinal or comparative analyses with repeated measures to determine participants’ progression). Initially, descriptive analyses of participants’ characteristics will be conducted, and the associations among research variables will be statistically analyzed (eg, Pearson correlations, partial correlations tailored to preliminary analyses, and group differences). We will use a method of controlling for additional variables that may influence statistical outcomes (eg, personal, medical, social, and demographic data) based on the results of the preliminary analyses.

The primary analysis (eg, participant randomization) will be based on the intention-to-treat principle. Missing data will be imputed using various techniques, and sensitivity calculations will compare the results to per-protocol analyses to determine the effect of dropouts.

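### The adverse-event scale mixes symptom with management need and ties its severe grade to leaving the study, which blurs safety reporting and may cost late STAI values

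*Protocol article*

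**What the plan says.** The grading rule is in the protocol article, Procedure, Data Monitoring. The lowest grade is a symptom description: "The severity of reported events will be classified as mild (transient discomfort". The other two are "moderate (requires temporary intervention modification), or severe (necessitates withdrawal from the study".

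On use of the data, the same section says: "All AEs and responses will be documented, reviewed in regular safety meetings, and included in the final study report". The monitoring board meets "to evaluate participant retention, dropout rates, and any reported adverse effects".

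On outcome timing, the abstract's Methods say: "Data will be collected at baseline, after the intervention, and during follow-up assessments". The Procedure overview adds that participants "complete an anxiety level assessment at the end of each intervention session", and the VR intervention section names the STAI as the end-of-session tool.

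On analysis, Data Analysis and Handling Missing Data says the primary analysis "will be based on the intention-to-treat principle", followed by: "Missing data will be imputed using various techniques, and sensitivity calculations will compare the results to per-protocol analyses to determine the effect of dropouts".

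**The concern.** A severity grade should say how bad an event was. What was done about it is a separate fact. Here the lowest grade describes the event and the upper two describe the response it calls for, so the three steps do not lie on one scale. At stake are two things.

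- **Safety reporting.** A table of events by grade, in the board's review or the final report, would not separate intense events from events that end participation. The severe row would say little that the dropout figures do not.
- **The primary outcome.** Because severe is linked to exit from the study, not just from the sessions, the participants who fared worst may have no post-program or follow-up STAI. Those values are unlikely to be missing at random.

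**Working it through.** This is mainly a check of the text. The article gives no figure for event rates, withdrawal rates or a dropout allowance, so there is no stated number on this point to reproduce.

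**Step 1: do the grades form one scale?** Apply the Data Monitoring definitions to four kinds of event.

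| Event | Grade under the stated rule |
|---|---|
| Brief discomfort, nothing changed | Mild |
| Brief discomfort that calls for a temporary change | Fits mild and moderate |
| Intense reaction that does not require withdrawal | Cannot be severe |
| Lasting distress or injury, referred for care, with no change to sessions and no withdrawal | No grade fits |

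The last row is not far-fetched: the same section foresees referral for lasting distress or injury. The grades are neither mutually exclusive nor exhaustive.

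**Step 2: what does the severe count measure?** Every severe event is, by definition, one that calls for withdrawal. The converse does not hold, because Ethical Considerations lets anyone leave at any time, including after an event that did not require it. Severe events are therefore close to a subset of event-related withdrawals. The two counts overlap heavily but need not be equal.

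**Step 3: withdrawal from what?** Data Monitoring speaks of the study. The VR intervention section speaks of dropping out of the support program after one month. The yoga section says only that non-completers count as withdrawn. The article uses both ideas but never says whether a participant who stops sessions is still assessed.

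**Step 4: what could be lost?** Baseline and end-of-session scores exist up to the point of exit. On the literal reading, the post-program and follow-up values would be missing.

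**Step 5: illustration of size.** The only design inputs are 30 per group, 80% power and 5% significance (Sample Size Determination). The effect size and SD are not given, so 30 cannot be re-derived. Assuming a two-sided test, the detectable difference is:

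(1.960 + 0.842) × √(2/30) = 0.72 SD (normal approximation), or 0.736 SD with the noncentral t.

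- One participant is 1/30 = 3.3% of an arm.
- Power at 0.736 SD with 0, 1, 3 or 6 lost from one arm (noncentral t): 80.0%, 79.3%, 77.8%, 75.1%.
- If a share *s* of an arm leaves and is *m* SD worse than those who stay, the full-arm mean exceeds the completer mean by *s* × *m*. The shares and excesses below are assumptions.

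| Share leaving | *m* = 0.5 SD | *m* = 1.0 SD |
|---|---|---|
| 1/30 | 0.017 | 0.033 |
| 5% | 0.025 | 0.05 |
| 10% | 0.05 | 0.10 |
| 20% | 0.10 | 0.20 |

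The article expects few events, so the top rows are the more plausible. The shift applies to a completer analysis. Under the planned imputation, the remaining bias depends on the method and cannot be computed here.

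**The case against.** The case on the other side is substantial, and much of it stands.

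- **A circular safety comparison.** A reader might infer that the trial's comparison of harms between arms is circular. No such comparison by severity is stated, and safety is not among the outcomes in the abstract. The point applies only to descriptive reporting by grade.
- **Severity as what the facilitator did.** The wording describes a judged need, not an action, and facilitators are named only as people to whom events are reported. Mild is symptom-based, so the scale is mixed rather than wholly action-based.
- **Complete overlap with withdrawals.** This does not follow, because voluntary withdrawal is allowed (step 2).
- **No safety information at all.** This is too strong. All events and responses are to be documented, and the board looks at dropout and adverse effects as separate items.
- **Outcome never measured.** This is also too strong. Scores up to exit exist, and no section says that assessment stops. The loss of later values is inferred from the wording.
- **Contradiction with intention-to-treat.** Analysis by randomized group is compatible with withdrawals, and imputation is planned. The principle is strained, not breached.

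It can also be said that log fields belong in a full protocol or event form that an article condenses. That does not answer this point: the grading rule is stated in the article, and the problem is how that rule works.

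**Conclusion.** The point holds in limited form and is of low severity. The Data Monitoring definitions mix symptom with management need. An intense event that does not require withdrawal cannot be graded severe, and the severe count largely repeats event-related withdrawals. Because severe is tied to the study rather than the sessions, participants with such events may lack the post-program and follow-up STAI. This makes the intention-to-treat analysis depend more on an imputation method that the article leaves open. The per-protocol comparison would not replace values that were never collected.

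The size is unknown. The 0.02 to 0.20 SD range rests wholly on assumed withdrawal shares and assumed excess anxiety, and the article's own expectation of few events points to the low end. The documents do not support a reading in which the safety analysis is void or the primary analysis contradicts itself.

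**What to change.** 1. In the event log, record two separate fields: intensity, graded by how strong the symptoms are and how far they interfere, and action taken (none, sessions modified, sessions stopped, left the study). Report both by arm.
2. Reconcile Data Monitoring, the VR intervention section and Data Analysis and Handling Missing Data so that stopping the sessions is distinguished from leaving the study. Align the yoga section's wording on withdrawal at the same time.
3. State that the post-program and follow-up STAI are still requested from participants who stop sessions and consent to further contact.

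When sessions are modified or stopped remains with the investigators; nothing here sets such a rule. The cost is one extra log field, a wording change and some follow-up contact.

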#### Auditing Procedures and Independence

To ensure adherence to protocol, data integrity, and participant safety, this study will undergo periodic internal audits conducted by an independent ethics and compliance committee at the 2 supporting academic institutions. Audits will occur at three key time points: (1) after initial participant enrollment, (2) midway through data collection, and (3) at the study’s conclusion before final analysis. The auditing process will assess protocol compliance, adherence to ethical guidelines, proper documentation of informed consent, accurate data collection procedures, and AE reporting. Any discrepancies or deviations identified during the audit will be reported to the principal investigator (PI) and the institutional review board (IRB) for corrective action. While this audit process is not fully independent from the sponsoring institution, it remains separate from the direct investigative team, reducing potential conflicts of interest. If significant concerns arise, an external auditor may be consulted to review trial conduct. The final audit findings will be documented in the study report and shared with regulatory authorities if required, ensuring transparency and research integrity.

### VR Cognitive Behavioral Intervention and Theoretical Background

The psychoemotional support intervention, facilitated by VR exposure techniques (6-10 sessions), uses Guided Meditation VR software and stand-alone Oculus Quest 2 and HTC Vive Flow hardware for alleviating performance anxiety. These consist of approximately 6 to 10 sessions of 20 to 30 minutes each of psychoemotional support based on cognitive behavioral techniques and integrative psychotherapy (with extension to a maximum of 1 h, if necessary). They will be carried out over a period of 2 weeks, up to a maximum of 1 month if it is not possible to organize the sessions in optimal conditions. After 1 month, the participants are reported as having withdrawn (in case of a request from the participants) or dropped out of the psychoemotional support program. The initial sessions (1-2 sessions) are designed for psychological assessment, psychoeducation, and familiarization with VR exposure techniques. In the next 2 to 3 sessions, different VR scenarios are tested to find a comfortable virtual environment for each patient. We test if patients agree that they are present in that generated virtual environment in a manner comparable to exposure in a natural environment (eg, a walk by the beach, in a forest, or an underwater itinerary). At this stage, subsequent exposure techniques will be developed using a combination of cognitive restructuring and relaxation methods, aimed at familiarizing participants with the technology and ensuring a pleasant experience. The next 1 to 2 sessions will continue with exercises already chosen, based on cognitive restructuring techniques combined with relaxation techniques. The last session is designed to review one of the exercises, assessing the quality of the technique and offering suggestions for improvement by going through a set of questions (eg, QoL through the QoL questionnaire). Each session concludes with a brief clinical assessment of anxiety using the State-Trait Anxiety Inventory (STAI) tool. Specific manifestations of performance anxiety are assessed.

VR-CBT represents an innovative psychotherapeutic intervention method in mental health, addressing traditional challenges by integrating VR technology to facilitate exposure and cognitive restructuring in a controlled, immersive environment. Frequently used for treating anxiety, phobias, obsessive-compulsive disorder, and depression, VR-CBT offers patients a captivating alternative where they can safely experience anxiety-inducing scenarios in a gradual and secure manner. Advantages and specific characteristics of VR-CBT based on recent studies detailing its applicability, benefits, and risks in managing mental health disorders and improving mental well-being are highlighted [25,26]. In recent years, VR-CBT has been recognized as a leading-edge technology in treating mental health disorders and is considered a significant innovation for mental well-being. For instance, the World Health Organization has included mental health in its global strategies, underscoring the need to develop innovative and accessible therapies for treating anxiety, depression, and related disorders [27]. Amid global challenges, such as the COVID-19 pandemic, VR-CBT promises to support traditional therapies by reducing physical and emotional barriers associated with exposure sessions [28].

A distinct feature of VR-CBT is its precise control over exposure. Unlike real-world exposure, VR allows therapists to create and customize therapeutic scenarios in a safe, repeatable environment while monitoring the patient’s physiological responses, including blood pressure and heart rate [29]. For instance, participants with social phobias can gradually be exposed to simulated social interactions, thereby reducing real-world anxiety and enhancing coping skills [30]. VR exposure aims to induce emotional responses such as those experienced in real situations but within a context where patients feel they can control and manage stressful scenarios. This increased control encourages patient compliance with therapy and reduces dropout rates, which is essential in treating complex mental disorders such as phobias and generalized anxiety [31].

Besides improving therapy compliance and effectiveness, VR-CBT significantly alleviates anxiety symptoms. Studies show that repeated and monitored exposure in VR environments helps reduce stress and anxiety levels in real-life situations [32]. For example, in a program for young people with anxiety disorders, VR therapy contributed to decreased anxiety levels and improved emotional regulation skills. Another notable advantage is VR’s ability to track patient gaze and reactions, which is an essential aspect for diagnosing symptoms that are difficult to observe, such as suspiciousness and misinterpretation of others’ intentions in psychotic disorders [33].

The effectiveness of VR-CBT was evaluated in an RCT where patients were divided into 2 groups; one group underwent VR therapy, and the other received traditional relaxation and meditation techniques [20]. The study showed a significant decrease in anxiety symptoms in the VR group, particularly regarding reduced somatic reactions and stress-related symptoms. These results suggest that VR-CBT can be an effective complementary method to conventional approaches, thereby reducing the need for anxiolytics and providing patients with long-term self-regulation techniques [34]. Furthermore, VR-CBT offers substantial potential for global application, being an accessible and cost-effective treatment option compared to conventional therapy. VR platforms are becoming more accessible, enabling increased access for patients who cannot participate in in-person therapies due to geographical barriers or severe anxiety [35].

### Yoga Intervention and Theoretical Background

This psychoemotional assistance intervention is facilitated through breathing techniques, meditation, and body postures (yoga). The program is designed to reduce anxiety and improve emotional well-being through a holistic mind-body approach. This program is a psychoemotional support intervention that incorporates yoga-based techniques, including breathing exercises, meditation, and body postures. The program runs for 2 to 4 weeks, depending on the scheduling of the sessions, with participants attending 6 to 10 sessions lasting 60 to 90 minutes each. If participants do not complete the program within 1 month, they are considered to have withdrawn.

The sessions include the following:

Body postures (asanas) that include a sequence of yoga postures such as Tadasana (mountain pose); Surya Namaskar (sun salutation); and various standing and seated poses such as the tree pose, warrior pose, and triangle pose, aimed at promoting physical alignment and relaxation.Breathing techniques (pranayama) that include exercises to control and expand the breath, such as Bhastrika (bellows breathing), Ujjayi (victorious breathing), and specific breath locks (Bandhas) to regulate energy flow.Meditation and relaxation that includes techniques such as Shavasana (relaxation pose) and chanting of the AUM mantra promote mental calmness and relaxation.

As described in Patanjali’s Yoga Sutras, Yama and Niyama represent 2 fundamental sets of ethical and moral rules within the yoga system. These principles, which form the foundation of any practitioner’s spiritual evolution, are intended for advanced yoga practitioners and beginners. Patanjali structured the yoga system into 8 progressive stages, known as ashtanga, which include Yama (rules for interacting with others) and Niyama (rules of inner discipline) as the first 2 steps of this system. Essentially, Yama and Niyama aim to guide the practitioner toward moral and spiritual balance, regulating both external and internal behavior. Following these principles is vital for reducing negative influences that may affect the practitioner, thus hindering spiritual growth and mental calm.

Yama, or the external moral rules, refers to the behaviors a yogi should adopt in relationships with others. These rules are ahimsa (nonviolence), satya (truthfulness), asteya (honesty), brahmacharya (sexual restraint), and aparigraha (nonpossessiveness). They form an ethical code governing practitioners’ thoughts, speech, and actions, with the purpose of preventing mental and emotional disturbances that can arise from unbalanced social interactions. For example, ahimsa, or nonviolence, refers to the absence of physical violence and nonviolence in thoughts and words. Practicing this rule leads to harmony in human relationships and, consequently, to mental calm.

Niyama, in contrast, governs the individual’s relationship with themselves. These rules are saucha (purity), santosha (contentment), tapas (discipline), svadhyaya (self-study and study of sacred writings), and ishvarapranidhana (devotion to divinity). Following these rules, the yogi cultivates inner harmony, thus reducing internal factors that block spiritual and mental progress. For instance, santosha, or contentment, encourages the practitioner to find peace and balance regardless of external circumstances, contributing to a significant reduction in stress and anxiety.

The practices described in Yama and Niyama are not merely abstract ethical codes but practical tools that directly influence emotion management and mental calmness. They offer a psychological discipline framework that facilitates internal and external conflicts, which ordinarily lead to emotional disturbances. In the Yoga Sutras, Patanjali argues that these rules are essential foundations for any progress in practice, allowing the establishment of a mental equilibrium that makes exploring higher stages of yoga possible, such as dhyana (deep meditation).

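### Participants who miss the 1-month limit are given a withdrawal status that is worded differently by arm and leaves them without a defined endpoint assessment; the per-protocol comparison cannot by itself show the effect

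*Protocol article*

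**What the plan says.** All references are to the protocol article.

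- **Yoga Intervention and Theoretical Background.** On duration: "The program runs for 2 to 4 weeks, depending on the scheduling of the sessions". On the limit: "If participants do not complete the program within 1 month, they are considered to have withdrawn".
- **VR Cognitive Behavioral Intervention and Theoretical Background.** On duration: "They will be carried out over a period of 2 weeks, up to a maximum of 1 month", the longer period being for sessions that cannot be arranged in good conditions. On the limit: "After 1 month, the participants are reported as having withdrawn (in case of a request from the participants) or dropped out". The sentence continues so that the second group is described as having "dropped out of the psychoemotional support program".
- **Procedure, Overview.** Anxiety is assessed after each session. The closing anxiety questionnaire is given when the program ends.
- **Abstract, Methods.** Data are collected at baseline, after the intervention and at follow-up. Intention-to-treat and sensitivity analyses are promised.
- **Data Analysis and Handling Missing Data.** The primary analysis follows intention-to-treat. On incomplete data: "Missing data will be imputed using various techniques". On dropout: "sensitivity calculations will compare the results to per-protocol analyses to determine the effect of dropouts".

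No section says whether someone classed as withdrawn or dropped out is still asked for the post-intervention and follow-up questionnaires.

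**The concern.** Stopping a treatment program and leaving a trial are different events. An intention-to-treat comparison relies on the first not causing the second. Here a participant's status follows from finishing sessions by a date, and in the yoga arm that status is withdrawn without qualification. The same behaviour in the VR arm is described as leaving the program. Site staff could reasonably stop contacting the yoga participant and keep contacting the VR participant.

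The post-intervention questionnaire is timed by the end of the program, so a non-completer in either arm has no date on which it falls due. The primary outcome is then left to imputation, although a self-report questionnaire could simply have been sent.

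The check offered for dropout is a comparison with per-protocol results. A per-protocol set excludes these same non-completers. If the imputation also learns only from completers, the two analyses can agree closely while both are biased. At stake is the between-arm contrast in anxiety, which is the purpose of the trial.

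**Working it through.** **The plan's own figure.** The article gives no dropout rate and no size for this effect. The only related number is 30 per group for 80% power at the 5% level. It cannot be reproduced, because no effect size or SD is stated. Inverting it with a two-sided two-sample t test gives an implied standardised difference of 0.736. That value is back-calculated and is used only in the last step.

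**The two rules side by side.**

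| | Yoga | VR |
|---|---|---|
| Planned length | 2 to 4 weeks | 2 weeks, up to 1 month |
| Sessions | 6 to 10 of 60 to 90 min | 6 to 10 of 20 to 30 min (up to 1 h) |
| Limit | 1 month | 1 month |
| Status after the limit | Withdrawn | Withdrawn on request, otherwise dropped out of the program |
| Endpoint for those past the limit | None defined | None defined |

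**Size of a possible bias.** Let p be the proportion of non-completers in an arm and g the amount, in SD, by which they fare worse than completers. The full-arm mean is the completers' mean plus p × g. Using completers alone therefore makes the arm look better by p × g. With the same g in both arms:

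bias in the contrast = (p_yoga − p_VR) × g

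Assumed inputs: p_VR = 10%, p_yoga = 10% to 30%, g = 0.5 to 1.0 SD.

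- 10% v 10%: 0 × g = 0
- 10% v 20%: 0.10 × 0.5 = 0.05 SD; 0.10 × 1.0 = 0.10 SD
- 10% v 30%: 0.20 × 0.5 = 0.10 SD; 0.20 × 1.0 = 0.20 SD

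With these inputs the bias favours yoga. If VR lost more, it would favour VR.

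**Simulation.** There were 400,000 participants per arm and no true difference. Non-completion was driven by a latent variable correlated 0.3 or 0.5 with a poor outcome.

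| Loss, VR v yoga | All outcomes collected | Completers only | Imputed from completers on baseline |
|---|---|---|---|
| 10% v 10% | about 0 | about 0 | about 0 |
| 10% v 20% | about 0 | 0.045 to 0.079 SD | 0.045 to 0.079 SD |
| 10% v 30% | about 0 | 0.089 to 0.149 SD | 0.089 to 0.149 SD |

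The last two columns agree because baseline was set to carry no information about the outcome. This shows that agreement with per-protocol does not rule out bias. It does not show that the two analyses must agree.

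**With session scores in the imputation.** Take 10% v 30%, a session score correlated 0.6 to 0.8 with the endpoint, and baseline correlated 0.5. Completers-only bias was about 0.05 to 0.15 SD. Imputation using session scores cut it to about 0.03 to 0.10 SD when loss depended on the endpoint itself, and to about 0 when loss depended on the session score.

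**Precision.** If 20% of endpoints were lost in each arm, 30 × 0.8 = 24 would remain, and power at the implied 0.736 would fall from 80% to 70.4%. If outcomes are collected regardless of completion, this rule costs nothing.

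**The case against.** The strongest reply is that a status label is not a data rule. Intention-to-treat concerns analysis as randomised. The article commits to it, expects dropouts and imputes their data. No section says that assessment stops, that data are discarded or that anyone leaves the analysis set. The VR sentence refers to leaving the program, not the trial, and the yoga sentence sits in a description of the intervention. All of this stands. A reader might infer that the rule contradicts intention-to-treat or deletes outcomes, but the text does not go that far. It leaves the endpoint undefined for these people.

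Anxiety is also measured after each session, so non-completers who attended have partial data. This stands too, and it reduces the possible bias. It does not replace an endpoint, because the scores stop when attendance stops.

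A reader might further infer that yoga will lose more participants. There are reasons to think so. At the session counts in Table 1, yoga takes 10 × 60 to 90 = 600 to 900 min and VR 9 × 20 to 30 = 180 to 270 min. The VR section credits VR with lowering dropout, and the Discussion ties yoga's benefit to sustained practice. But the limit and the 6 to 10 sessions are common to both arms, and no rates are given. Unequal loss is plausible, not established.

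Finally, the imputation method and primary model are commonly left to an analysis plan. That is right, and neither is criticised here. Continued outcome collection is different, because an analysis plan cannot recover questionnaires that were never sent.

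**Conclusion.** The point holds in a limited form. The article sets a completion-based withdrawal status, words it differently in the two arms, and defines no endpoint assessment for those it catches. That undermines the intention-to-treat analysis without contradicting it. The per-protocol comparison is a weak check and cannot by itself establish what dropout did to the result.

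The size is conditional. Bias between arms requires loss that is both outcome-related and unequal. At an assumed 10% in VR and 20% to 30% in yoga, with non-completers 0.5 to 1.0 SD worse, it is about 0.05 to 0.20 SD among completers. It is less if session scores inform the imputation, and about 0 with equal loss. None of these rates or gaps comes from the article. This is a cheap improvement best made before enrolment, not evidence that the planned analysis is invalid. The grading of severe adverse events by study withdrawal is a separate matter.

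**What to change.** - Leave the 1-month limit as it is. Describe its consequence in the same words in both intervention sections: the participant has stopped the program and remains in the study. Reserve withdrawal from the study for participants who withdraw consent.
- Collect the STAI at post-intervention and follow-up times fixed from randomisation, for all randomised participants unless they withdraw consent.
- State that all randomised participants are analysed as allocated.
- Add a sensitivity analysis for data missing not at random, for example delta-adjusted imputation with the shift allowed to differ by arm.
- Keep the per-protocol analysis as supplementary, and drop the claim that it determines the effect of dropouts.

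The cost is a few sentences and reminders to non-completers for a self-report questionnaire.
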